### Study design and setting

The study design is a multicenter, prospective interrupted time series (Fig. 1), which will take place in seven hospitals in the Netherlands (three university and four general hospitals). We aim to reduce 25–50% of the catheters without an appropriate indication by a de-implementation strategy of multiple interventions. The clinical data collection will be once per 14 days during 8 months in both the pre- and post-intervention period. During these measurement days all patients with a urinary and/or (peripheral and/or central) intravenous catheter inserted during the hospital stay will be enrolled. The de-implementation strategies will start during a transition period of 4 months, while no patients will be included.

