### Sample size

The sample size is based on the objective of a 25–50% reduction in the number of invalid indications for both urinary and peripheral intravenous catheters, with a power of 80% and an alpha of 0.05. We excluded CVCs in the sample size, since the use of CVCs in the internal medicine and subspecialties departments is infrequent, but we will include all patients with a CVC in the study. We used the incidence of inappropriate use of the catheters from previous results in similar healthcare systems, which is 40% in urinary catheters [2, 20] and 50% in PIVC [13]. This results in 91–376 patients with a urinary catheter, and 66–284 patients with a PIVC. Correlating for 10–15% missing data the sample size is set to respectively 105–410 and 75–300 patients in both pre- and post-intervention group. This will result in a total sample size of 210–820 patients with a urinary catheter and 150–600 patients with a PIVC. We aim to include this number of patients in each hospital to evaluate the effect of the interventions in each individual hospital.

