### Statistical analysis

Effect evaluation will be performed using SPSS statistics 23. Categorical variables will be presented as frequencies and percentages, and continuous variables as means (with a standard deviation) or medians (with an interquartile range) depending on the data distribution. We will use segmented regression analysis of interrupted time series methods to evaluate the differences between the baseline and intervention group [34, 35]. The data will be adjusted for possible confounders, autocorrelation and the underlying secular trend. We will perform stratified analyses to evaluate the impact of the de-implementation strategy in subpopulations. Figures will be used to visualize the underlying secular trend and the impact of the de-implementation strategy. The difference will also be presented in unadjusted and adjusted rate ratio (RR) with a 95% confidence interval (CI). Differences are considered to be statistically significant with a *p* < 0.05.

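### The per-hospital sample sizes give 80% power for a simple before/after comparison; the trend-adjusted segmented regression has only about 18–22% at the same pairings of effect and size

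*Protocol article*

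**What the plan says.** The Sample size section starts from a 25–50% relative reduction, "with a power of 80% and an alpha of 0.05", with 40% inappropriate use assumed for urinary catheters and 50% for PIVCs. It reports: "This results in 91–376 patients with a urinary catheter, and 66–284 patients with a PIVC". After an allowance for missing data the targets per period become 105–410 and 75–300. The section closes by attaching them to single hospitals: "We aim to include this number of patients in each hospital to evaluate the effect of the interventions in each individual hospital".

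The Statistical analysis section names segmented regression of the interrupted time series as the way to evaluate the difference, and adds: "The data will be adjusted for possible confounders, autocorrelation and the underlying secular trend". Unadjusted and adjusted rate ratios with 95% confidence intervals are to be presented as well, and significance is set at p < 0.05.

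Study design and setting fixes the schedule: one measurement day every 14 days for 8 months before and 8 months after, and between them a break: "The de-implementation strategies will start during a transition period of 4 months, while no patients will be included".

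**The concern.** The sample size calculation uses no time points, trend, autocorrelation or gap. It treats each hospital as two independent groups of patients. The named analysis separates the intervention effect from a time trend. On this schedule, time and the before/after indicator are strongly correlated, so much of the information in the simple comparison is lost. The stated 80% therefore does not carry over to the trend-adjusted effect in one hospital.

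At stake is how hospital-level results are read. If each hospital is judged at p < 0.05, most would probably show no significant change even where the strategy achieves its target, and this could be taken as local failure.

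**Working it through.** **1. Reproducing the plan's sizes.** With p̄ the mean of p₁ and p₂:

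n₀ = [1.96·√(2p̄(1−p̄)) + 0.8416·√(p₁(1−p₁)+p₂(1−p₂))]² / (p₁−p₂)², and with continuity correction n = (n₀/4)·[1 + √(1 + 4/(n₀|p₁−p₂|))]².

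For 40% vs 30%: n₀ = (1.3220 + 0.5646)²/0.01 = 355.9, and n = 88.99 × 2.0547² = 375.7, so 376. The same formula gives 91 for 40% vs 20% and 66 for 50% vs 25%. For 50% vs 37.5% it gives 262; the stated 284 appears when 37.5% is rounded to 38%. The test is taken as two-sided, which the protocol does not state but which fits the figures.

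**2. Variance of the trend-adjusted level change.** Inputs from Study design and setting: 17 points spread over months 0–8 and 17 over months 12–20 (8 months at 14-day intervals is about 17 visits). Assumptions: equal numbers per visit, a constant effect, no true trend, independent binomial errors.

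- Within-period variance of time: 0.5² × (17² − 1)/12 = 6.
- Period centres are at months 4 and 16, 12 months apart, so the between-period variance is 6² = 36.
- Squared correlation of time with the indicator: 36/42 = 0.857. Variance inflation with a common slope: 1/(1 − 0.857) = 7.0.
- With a slope change and the effect read at month 12: [(1 + 8²/6) + (1 + 4²/6)]/2 = (11.667 + 3.667)/2 = 7.67.

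**3. Power per hospital.** Write v₁ = p₁(1−p₁), v₂ = p₂(1−p₂) and n for patients per period. With binomial weights:

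- common slope: Var = [v₁ + v₂ + (12²/6)/(1/v₁ + 1/v₂)]/n
- level and slope change: Var = (11.667·v₁ + 3.667·v₂)/n
- power = Φ(|p₁−p₂|/SE − 1.96) + Φ(−|p₁−p₂|/SE − 1.96)

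For urinary 40% vs 30%, n = 376, common slope: Var = (0.45 + 2.688)/376 = 0.00835, SE = 0.0914, ratio 1.095, power 19.5%.

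| Stated pairing | n per period | Common slope | Level + slope change |
|---|---|---|---|
| Urinary 40% → 20% | 91 | 21.3% | 17.9% |
| Urinary 40% → 30% | 376 | 19.5% | 17.7% |
| PIVC 50% → 25% | 66 | 21.6% | 18.8% |
| PIVC 50% → 37.5% | 284 | 20.8% | 19.2% |

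The 95% half-width for urinary catheters at n = 376 (common slope) is 1.96 × 0.0914 = ±18 points, against 1.96 × √(0.45/376) = ±7 in the simple comparison.

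**4. How far the assumptions matter.**

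- AR(1) autocorrelation of 0.2 between fortnightly points: about 14–17%.
- A slightly wider spacing of the visits around the gap: 17.8–19.7% (common slope) and about 15–18% (slope change). Simulated logistic segmented regressions on that spacing gave 16–20%.
- Ignoring the 4-month gap, contrary to the schedule: at most about 38%, even at the missing-data-inflated targets.
- A 50% reduction at the upper-end sizes (376–410 urinary, 284–300 PIVC): about 56–70% before autocorrelation.
- 80% power with a common slope at the wider spacing: about 597 / 2,773 urinary and 426 / 1,916 PIVC patients per period, 6.5–7.4 times the stated sizes.

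**5. Pooled over seven hospitals.** At 7 × 376 = 2,632 and 7 × 284 = 1,988 per period, for a 25% reduction, the formulas in step 3 give about 78–86%. AR(1) of 0.1–0.2 lowers this to about 64–80%. The wider spacing with a slope change gives 71–76% with independent errors.

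**The case against.** Several points on the other side are sound and limit what can be said.

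- A reader might infer that the 80% belongs to an analysis that will never be done. The Statistical analysis section does not support this: an unadjusted rate ratio will also be presented, and the sample size fits that comparison. It is secondary to the segmented regression, however, and relying on it would give up the control for trend that an uncontrolled before/after design needs.
- A reader might infer that one hospital would miss a 50% reduction about four times in five at any planned size. That holds only at the lower-end sizes; at the upper end, power for that effect is about 56–70%.
- A reader might infer that the primary analysis is seven separate tests per catheter type. No section says so. Hospital-level evaluation appears only as an aim in the Sample size section.
- The article does not give the regression terms, the tested parameter or the autocorrelation structure, and may leave them to a fuller document. The 18–22% is therefore conditional. At the stated pairings, though, no trend-adjusted version examined exceeds about 38%.
- The sizes are targets, not caps, since all eligible patients on measurement days are enrolled. This softens the figures, but about seven times the target would be needed.

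**Conclusion.** The point holds for the hospital-level aim. The protocol attaches 80% power to evaluation in single hospitals, and its named analysis does not deliver that at the stated pairings of effect and size. Power is about 18–22% with 17 + 17 points, the 4-month gap, a linear trend and independent binomial errors, and lower with positive autocorrelation.

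The documents do not support the wider conclusion that the study as a whole is badly underpowered. Pooled over seven hospitals at the upper-end sizes, the segmented regression comes close to 80% under independent errors. A flat 80% would nevertheless be unsupported there too, because the plan itself adjusts for autocorrelation.

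**What to change.** In Sample size:

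- State that the 80% power refers to the unadjusted comparison of two proportions.
- Add that the trend-adjusted segmented regression has roughly 15–22% power per hospital at the paired sizes, and list the assumptions (number of points, gap, linear trend, error structure).
- Give pooled power as a conditional range: about 78–86% with independent errors and about 64–80% with AR(1) of 0.1–0.2, at seven times the upper-end sizes.

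In Statistical analysis:

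- Base the main conclusion on the segmented regression pooled over the seven hospitals.
- Present hospital-level segmented-regression results as estimates with 95% confidence intervals, and state that a non-significant hospital result is not to be read as no effect.

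The cost is a rewording of two paragraphs and a less favourable stated power. No extra patients or data are needed.

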### Statistical analysis

Effect evaluation will be performed using SPSS statistics 23. Categorical variables will be presented as frequencies and percentages, and continuous variables as means (with a standard deviation) or medians (with an interquartile range) depending on the data distribution. We will use segmented regression analysis of interrupted time series methods to evaluate the differences between the baseline and intervention group [34, 35]. The data will be adjusted for possible confounders, autocorrelation and the underlying secular trend. We will perform stratified analyses to evaluate the impact of the de-implementation strategy in subpopulations. Figures will be used to visualize the underlying secular trend and the impact of the de-implementation strategy. The difference will also be presented in unadjusted and adjusted rate ratio (RR) with a 95% confidence interval (CI). Differences are considered to be statistically significant with a *p* < 0.05.

### Economic evaluation

The main question for the economic evaluation is if the benefits of a reduction in inappropriate use of catheters, which probably lead to a reduction in catheter-related infections, length of stay and associated costs, outweighed the costs associated with this de-implementation strategy. For feasibility reasons, we will use length of stay on general and ICU wards, readmission within 30 days of discharge, catheter-related complications, representing the main features of the healthcare system, and productivity costs for societal perspective. We will estimate the unit costs for healthcare service based on the prices in the Dutch guideline on healthcare costs [36]. We will divide the de-implementation costs in non-recurrent and recurrent costs. The non-recurrent costs are study-related, such as the costs of development of the de-implementation strategy, material costs, and costs of evaluation of the de-implementation. Recurrent costs are the costs to implement the de-implementation strategy. The primary analysis is a cost-effectiveness analysis, in which the difference in costs of the de-implementation and outcomes between the baseline and intervention group will be estimate using incremental cost-effectiveness ratios (ICERs). The cost-benefit analysis will be reported as the ratio of de-implementation costs to reduction of healthcare costs (de-implementation costs < reduction healthcare costs). Statistical uncertainty will be evaluated in sensitivity analyses, such as unit costs, preference weights, estimates of effectiveness and discount rate. The result from the economic evaluation will be extrapolated to the national level using a budget impact analysis according to the principles of the report of the International Society for Pharmacoeconomics and Outcome Research Task Force [37], conducted from societal perspective and health insurance or national health service perspective.

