### Primary and secondary endpoints

The primary endpoint is the percentage of patients with an inappropriate indication for urinary and intravenous catheter on the days of data collection. Secondary endpoints are catheter-related infections and other complications, catheter reinsertion rate, use of antibiotics, length of hospital stay (and ICU) in days, in hospital mortality, and costs of the de-implementation strategy and the main healthcare costs.

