### Assessments

The presence and indications for the catheter use will be extracted from the medical records in combination with observations of the admitted patients. During the day of measurement the indication of the urinary and/or intravenous catheter and some patient variables will be collected. If there is an unclear indication of a catheter, the investigator will contact one of the healthcare workers (HCWs) to verify this information.

After discharge, the occurrence of catheter-related infections (see Table 3 for definitions) [31], with diagnostics and treatment, or other catheter-related complications (measured in registry and by investigator), the number of catheter days, reinsertion rate, use of alternatives for an indwelling urinary catheter (continence garments, condom catheters, intermittent straight catheterization), reason for admission, Charlson comorbidity index [32], duration of hospital (and ICU) stay, readmission within 30 days after discharge, and mortality (in hospital or within 30 days after discharge) will be collected from (electronic) medical- and nursing records. Furthermore, the nurse-to-patient ratios and the clinical work experience of residents will be collected.

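### The cost list omits reinsertions, urinary-catheter alternatives and catheter days, although all three are already collected, so the cost difference may be biased in a direction that cannot be known in advance

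*Protocol article*

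**What the plan says.** The Economic evaluation section of the protocol article names its resource items. Giving feasibility as the reason, it states "we will use length of stay on general and ICU wards, readmission within 30 days of discharge, catheter-related complications, representing the main features". It adds productivity costs for the societal perspective. On prices it says "We will estimate the unit costs for healthcare service based on the prices in the Dutch guideline on healthcare costs". The expected mechanism is that less inappropriate use will bring benefits, "which probably lead to a reduction in catheter-related infections, length of stay and associated costs".

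The resulting costs feed an incremental cost-effectiveness ratio, a cost-benefit measure defined as the "ratio of de-implementation costs to reduction of healthcare costs", and a national budget impact analysis.

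The Assessments section lists what is taken from the records after discharge. This includes "the number of catheter days, reinsertion rate" and, continuing, "reinsertion rate, use of alternatives for an indwelling urinary catheter (continence garments, condom catheters, intermittent straight catheterization". The Primary and secondary endpoints section also names "catheter reinsertion rate, use of antibiotics, length of hospital stay (and ICU) in days" among the secondary endpoints. Neither section links reinsertions, alternatives or catheter days to the economic evaluation.

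**The concern.** The strategy works by getting catheters taken out, or not put in. Its most immediate resource effects are fewer catheter days (materials and nursing time), possibly some catheters that have to be replaced, and possibly more use of continence garments, condom catheters or intermittent catheterisation. None of these is costed. The listed items lie mostly further downstream.

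Difficulty of data collection does not explain the gap, because the study already plans to extract all three items. Use of alternatives is collected but appears in no stated endpoint and no described analysis.

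At stake is whether the cost difference is complete. It decides whether the strategy is judged cost-saving, and it is scaled up to the country. The sensitivity analyses named as examples (unit costs, preference weights, effectiveness, discount rate) do not vary which items are counted, so they would not reveal the effect of the omission.

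**Working it through.** The protocol states no cost, saving or cost-effectiveness ratio, so there is no figure to reproduce. The check compares the lists and then gauges orders of magnitude.

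**1. Items side by side**

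| Item | Measured? | On the cost list? | Direction given in the protocol |
|---|---|---|---|
| Ward and ICU stay | Yes | Yes | Probably down |
| 30-day readmission | Yes | Yes | None stated |
| Catheter-related complications | Yes | Yes | Down |
| Reinsertions | Yes (secondary endpoint) | No | None stated |
| Alternatives to a urinary catheter | Yes | No | None stated |
| Catheter days | Yes | No | Down (Objectives) |
| Antibiotic use | Yes (secondary endpoint) | Not separately | None stated |

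The omissions fall on both sides: reinsertions and alternatives could add cost, while fewer catheter days save it.

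**2. Pilot inputs** (Background, intervention studies)

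- Catheter days per patient: 1009/74 = 13.64 before and 672/75 = 8.96 after, a fall of 4.68.
- Infections: 4 per 1000 catheter days before and 0 after, so at most 0.004 × 13.64 = 0.055 infections avoided per patient.
- Median stay: 13 to 9 days, a fall of 4. Costs depend on the mean, so this is only a proxy.

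The euro prices, percentages and days per infection below are assumptions; the protocol gives none.

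**3. Alternatives.** Suppose 20% to 40% of patients need one on the days freed, at EUR 15 to 40 per day.

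- Low: 0.20 × 4.68 × 15 = EUR 14 per patient.
- High: 0.40 × 4.68 × 40 = EUR 75 per patient.

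This leans high if part of the 4.68 days is simply earlier discharge. It applies to urinary catheters only.

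**4. Reinsertions.** Suppose a rise of 5 to 20 percentage points, each costing the equivalent of 0.05 to 0.2 bed-day: 0.05 × 0.05 = 0.0025 to 0.20 × 0.2 = 0.04 bed-day per patient. That is 0.06% to 1% of a 4-day fall. At EUR 300 to 600 per bed-day it is EUR 0.75 to 24.

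**5. Direction.** Let c be the cost of materials and handling per catheter day. The omitted saving is 4.68 × c. It cancels the omitted costs when

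- low: c = (14 + 0.75)/4.68 ≈ EUR 3;
- high: c = (75 + 24)/4.68 ≈ EUR 21.

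If a catheter day costs more than this break-even, the short list understates the net saving; if less, it overstates it. The protocol gives nothing to decide between the two.

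**6. Size relative to stay.** A 4-day fall at EUR 300 to 600 per bed-day is EUR 1,200 to 2,400. The alternatives are then 14/2,400 = 0.6% to 75/1,200 = 6% of it. If stay fell by only 0.25 day (EUR 75 to 150), the same items would be 14/150 = 9% to 75/75 = 100%.

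**7. Overlap of stay and complications.** If each infection adds 1 to 5 bed-days and its price includes them, 0.055 to 0.27 bed-day per patient is counted twice, or 1.4% to 6.8% of a 4-day fall. If the price excludes stay, nothing is.

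**The case against.** The restriction is declared: the section opens its list with "For feasibility reasons, we will use length of stay on general and ICU wards", and the endpoints promise only the main healthcare costs. Confining an evaluation to its main drivers is a legitimate choice. If stay falls as in the pilot, it dominates the result and the omitted items hardly matter. The protocol records use of alternatives but does not say that it records days on each one, so costing them by day may need information that the records do not give.

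Much of this stands. It limits the size of the point and means that alternatives may have to be costed per use. It does not remove the point: reinsertions and catheter days are recorded, and a stay effect as large as the pilot's, from an uncontrolled before-and-after comparison of 149 patients, cannot be relied on.

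A reader might go further and infer that the list keeps what falls and drops what rises, so that net savings are overstated. The documents do not support that. Nowhere do they say that reinsertions or alternatives will increase. Catheter days, an expected saving, are also left out, and antibiotic use is not separately listed. Readmission is on the list and could capture harm.

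A reader might also infer that stay is counted twice. That depends on what the complication price contains, which the article does not say and which a condensed article may leave to the full economic plan.

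**Conclusion.** The point holds as one of completeness. The fixed cost list omits direct catheter-related resources that the study already collects, so the cost difference and everything built on it may be biased, with a sign that cannot be determined beforehand.

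The effect is probably small, a few per cent of the stay saving, if the pilot's fall in stay recurs. It could approach the size of the counted stay saving if stay barely moves. These sizes rest on the pilot's catheter days and median stay and on assumed prices and frequencies, so they show order of magnitude only. Possible double counting of stay does not carry the finding, but it should be settled when the list is revised.

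**What to change.** Add three items to the healthcare cost list, in the main analysis or at least in a named sensitivity analysis:

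- reinsertions, by catheter type;
- recorded use of alternatives to an indwelling urinary catheter, costed per use, or per day where the records give days;
- catheter days, covering materials and handling.

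Taken together, these count offsetting costs and savings alike. In the same revision, state that complications are priced net of bed-days (diagnostics, treatment and procedures only), so that stay enters once.

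The cost is a few extra unit prices applied to data already planned for collection. The reported net saving may move slightly in either direction.

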### Patient selection

We will include all patient (≥18 years old) admitted to internal medicine and subspecialties (gastroenterology & hepatology, geriatrics, pulmonology and rheumatology) and all nonsurgical patients admitted to acute medical units, who receive urinary and/or (peripheral and/or central) intravenous catheter. Patients admitted for elective short stay, terminally ill patients and patients who had all catheters prior to admission will be excluded (Fig. 2).

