### De-implementation strategy

We will use a bundle of interventions (Table 4), since it is known that multiple and well-organized interventions result into better improvements. The main intervention is the dissemination of the list of appropriate indications (Table 1), which will restrict the insertion of urinary and intravenous catheters by physicians and nurses. The recommendation will be to remove the catheters without or with an expired valid indication. A local ‘champion’ (one of the leading physicians) will be appointed to be responsible for the interventions in his or her department. The intervention period will start with a kick-off meeting, where a list of baseline data of the intervention hospital in comparison with the other study hospitals will be presented as a competitive feedback report [33]. If desired, feedback reports per department could be sent by e-mail to local investigators. Thereby two educational meetings about insertion, care and maintenance of urinary and intravenous catheters will be applied to change HCWs behavior. Furthermore, HCWs will be encouraged and reminded to remove inappropriate catheters by posters, pocket cards and e-mail messages. In addition to other studies, patients will be actively supported by education material to participate in their treatment.

**Table 4 Tab4:** De-implementation strategy

Interventions of de-implementation strategy
List of appropriate indications
Local ‘champion’
Kick-off meeting, including competitive feedback report of baseline data
Education meeting for healthcare workers
Education materials (e.g., posters, pocket cards)
Patient education materials
Optional interventions based on baseline data and local conditions per hospital

Subsequently, all impeded and promoted factors of this de-implementation strategy for both HCWs and patients will be evaluated by direct observations and interviews. Additional prevention strategies could be applied based on these affecting factors and local conditions in the different hospitals.

If this de-implementation strategy prove to be effective, persistent awareness of the local ‘champion’ in combination with recurrent surveillance of the appropriate use of catheters and catheter-related infections will improve the sustainability. Thereby the de-implementation rule “No indication = Remove catheter” will be recommended in national guidelines and local protocols.

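### Secondary outcomes and the ICER compare only patients found with a catheter on a survey day, a group whose make-up the strategy itself changes

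*Protocol article*

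**What the plan says.** Under Study design and setting, the protocol article states: "The clinical data collection will be once per 14 days during 8 months in both the pre- and post-intervention period". Enrolment follows from that survey: "During these measurement days all patients with a urinary and/or (peripheral and/or central) intravenous catheter inserted during the hospital stay will be enrolled". Patient selection repeats the condition by limiting the study to ward patients "who receive urinary and/or (peripheral and/or central) intravenous catheter".

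The secondary endpoints include catheter-related infections and other complications, reinsertion, antibiotic use, "length of hospital stay (and ICU) in days, in hospital mortality, and costs of the de-implementation strategy and the main healthcare costs". Under Assessments, most of these, together with readmission, are collected from records after discharge. The Economic evaluation section compares the same two groups: "the difference in costs of the de-implementation and outcomes between the baseline and intervention group will be estimate using incremental cost-effectiveness ratios (ICERs". The result is then extrapolated nationally in a budget impact analysis.

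The De-implementation strategy section describes an indication list "which will restrict the insertion of urinary and intravenous catheters by physicians and nurses", and adds: "The recommendation will be to remove the catheters without or with an expired valid indication". The Objectives expect fewer catheter days.

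The Statistical analysis section plans segmented regression with adjustment for confounders, autocorrelation and secular trend. The Discussion names two limitations, the missing control group and the inability to separate single interventions. It does not mention selection into the sample.

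**The concern.** Membership of the intervention group depends on having a catheter on a survey day, which is exactly what the strategy sets out to change. Two things follow.

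- **Case mix.** If inappropriate catheters are avoided or removed, the patients who would have carried them are under-represented afterwards. Those who remain are more often patients who need a catheter. Mean stay, mortality and cost among the enrolled can move although no patient's outcome has changed.
- **Length-biased sampling.** A survey every 14 days catches long catheterisations more often than short ones. When dwell time shortens, the chance of being caught falls, and it falls unequally across patients.

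Both shifts begin when the strategy begins, so a segmented regression would read them as part of the intervention effect. Adjusting for patient characteristics can reduce a measured imbalance among the enrolled, but it cannot bring back patients who were never enrolled. At stake are the clinical secondary outcomes and the cost-effectiveness result meant to support a nationwide approach.

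**Working it through.** **Inputs from the protocol article.** Inappropriate use at baseline is 40% for urinary catheters and 50% for PIVCs (Sample size). The target is a 25–50% reduction in the number of catheters without an appropriate indication (Objectives). The survey interval is 14 days (Study design and setting). Pilot catheter days fell from 1009 in 74 patients to 672 in 75 (Background, intervention studies).

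**The plan's own figures.** The article gives no figure for this bias. The planning percentages can be confirmed from the sample sizes. With two-sided alpha 0.05, 80% power and a continuity correction, 40% vs 20% gives 91, 40% vs 30% gives 376 and 50% vs 25% gives 66, as stated. The stated 284 is reproduced by 50% vs 38%, that is, with 37.5% rounded up.

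**Step 1: change in mix.** Take 100 enrolled patients with one catheter each (assumption), a baseline inappropriate share *q*, and a proportion *r* of inappropriate catheters removed from the sample. The new share is *q*(1 − *r*)/(1 − *qr*).

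| Catheter | *r* | Still enrolled | Inappropriate share | Fall in share |
|---|---|---|---|---|
| Urinary, *q* = 0.40 | 0.25 | 90 | 30/90 = 33.3% | 0.067 |
| Urinary, *q* = 0.40 | 0.50 | 80 | 20/80 = 25.0% | 0.150 |
| PIVC, *q* = 0.50 | 0.25 | 87.5 | 37.5/87.5 = 42.9% | 0.071 |
| PIVC, *q* = 0.50 | 0.50 | 75 | 25/75 = 33.3% | 0.167 |

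**Step 2: shift in mean stay with no true effect.** The shift equals the fall in share times the gap in mean stay between patients with appropriate and inappropriate indications. The gap is not in the documents; 2–6 days is assumed.

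- Urinary, gap 2 days: 0.067 × 2 = 0.13 to 0.15 × 2 = 0.30 days.
- Urinary, gap 6 days: 0.067 × 6 = 0.40 to 0.15 × 6 = 0.90 days.
- PIVC, gap 2 days: 0.071 × 2 = 0.14 to 0.167 × 2 = 0.33 days.

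Mean stay rises if appropriately catheterised patients stay longer and falls if they stay less long.

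**Step 3: chance of being sampled.** Mean catheter days in the pilot were 1009/74 = 13.6 before and 672/75 = 9.0 after. Treating each mean as one dwell period shared by all patients (assumption), the chance of being caught by a 14-day survey falls from 13.6/14 ≈ 97% to 9.0/14 = 64%.

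**Step 4: simulation of the survey.** Each patient's stay was held fixed and only excess catheter time was cut, by 0%, 25% and 50%. The stay and dwell distributions are assumed.

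| Scenario | True mean stay | Sampled, 0% | Sampled, 25% | Sampled, 50% |
|---|---|---|---|---|
| A | 7.67 days | 11.14 | 11.30 | 11.44 |
| B | 8.50 days | 11.62 | 11.93 | 12.24 |

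With no true change, sampled mean stay moves by up to 0.30 days in A and 0.62 days in B.

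**The case against.** Several counter-arguments have force.

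- **Later removals are captured.** A reader might infer that every saving or harm in de-catheterised patients is invisible. The documents do not support that. Outcomes are collected after discharge, so a patient enrolled with a catheter that is later removed stays in the data. The pilot suggests that this matters, since most urinary indications were valid at first and lapsed after 2–3 days. Only avoided insertions and removals before a survey day are lost.
- **Losing one catheter need not end enrolment.** A patient whose urinary catheter is removed but who keeps a PIVC remains enrolled. The Background cites a study in which 81.9% of internal medicine patients had a PIVC. The one-catheter illustration is therefore diluted in practice.
- **The gaps are assumed.** A reader might also infer a known bias of a given sign. Nothing in the documents fixes one, and the simulated shifts are about 3–5% of mean stay at the 50% end.
- **Indication and comorbidity are recorded.** Stratifying by recorded indication would expose the mix shift in step 2. It would not restore unsampled patients or remove the length bias.
- **Uncertainty of the ICER.** From "Statistical uncertainty will be evaluated in sensitivity analyses, such as unit costs, preference weights, estimates of effectiveness and discount rate" a reader might infer that sampling error is ignored, or that preference weights have no data behind them. The list is open-ended and the article is condensed, so neither inference is supported.

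What remains is the structural point: both the enrolment rule and the comparison are stated, and selection changes when the strategy starts.

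**Conclusion.** The concern holds as a partial selection problem in the clinical secondary outcomes and the economic evaluation. The before-and-after contrast conditions on having a catheter on a survey day, which the strategy is designed to alter, and the planned adjustment and segmented regression cannot repair that.

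Its size and direction cannot be determined from the documents and may differ by outcome. For urinary catheters the illustration gives a spurious shift in mean stay of 0.07–0.15 times the gap in stay, or 0.13–0.9 days for gaps of 2–6 days. It rests on one catheter per patient, full exit from the sample when that catheter goes, and an assumed gap. Patients who keep another catheter make it smaller.

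The conclusion takes the enrolled catheter patients to be the population for the post-discharge outcomes. The Assessments section does not restate the population, but the article describes no other. The primary endpoint is a separate matter and is not judged here.

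**What to change.** 1. For hospital stay, ICU stay, readmission, mortality and the costs derived from them, use routine admission data on all adult admissions to the study wards in both periods, with or without a catheter. Do not restrict this to patients present on survey days, because that sample would still over-represent long stays.
2. Analyse these outcomes with the segmented regression already planned.
3. Build the ICER and the budget impact per ward admission from those results.
4. Label infections, complications, reinsertion and any other comparison limited to enrolled catheterised patients as descriptive and conditional on catheterisation on a survey day. Draw no causal or cost-saving conclusion from them.
5. Add this selection to the limitations in the Discussion.

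**Cost.** One routine extract per hospital and a change of wording in the analysis and economic sections. The effect per patient will look smaller, because patients who never had a catheter are included. Eligibility for these outcomes has to be worded without the catheter condition, and exclusions such as terminal illness may be applied only approximately in routine data.
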